**Methods/design:**

This multicenter parallel open-label cluster randomized controlled trial is composed of three phases: I, baseline phase in which retrospective data are collected, quality of data recording in facility registers is checked, and expected acceptability and feasibility of the intervention is assessed; II, intervention phase with enrolment of index cases and contact cases in either facility- or community-based models; and III, explanatory phase including endpoint data analysis, cost-effectiveness analysis, and post-intervention acceptability assessment by healthcare providers and beneficiaries. The study uses both quantitative and qualitative analysis methods. The community-based intervention includes identification and screening of all household contacts, referral of contacts with TB-suggestive symptoms to the facility for investigation, and household initiation of preventive therapy with follow-up of eligible child contacts by community healthcare workers, i.e., all young (< 5 years) child contacts or older (5–14 years) child contacts living with HIV, and with no evidence of TB disease. Twenty clusters representing TB diagnostic and treatment facilities with their catchment areas are randomized in a 1:1 ratio to either the community-based intervention arm or the facility-based standard of care arm in Cameroon and Uganda. Randomization was stratified by country and constrained on the number of index cases per cluster. The primary endpoint is the proportion of eligible child contacts who initiate and complete the preventive therapy. The sample size is of 1500 child contacts to identify a 10% difference between the arms with the assumption that 60% of children will complete the preventive therapy in the standard of care arm.

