### Cluster selection and randomization

The study clusters are health facilities supported by the CaP TB Program with TB diagnostic and treatment capacity after an initial assessment taking into consideration the number of bacteriological index cases identified from January to December 2018 (minimum of 50). Priority was given to rural, semi-rural, or semi-urban facilities as there is less population movement than in an urban setting with relatively easy access. In Cameroon, there were mainly district hospitals because TB diagnosis is mainly done at the secondary healthcare level, with ten clusters selected from two regions (Central and Littoral regions). In Uganda, as TB services are decentralized at the primary healthcare level, the ten clusters were primary health centers in four districts in the South West region, some with two facilities per cluster in order to reach the minimum of 50 index cases per year.

The randomization was stratified by country, and in each country, the 10 clusters have been allocated to one of the study models by a covariate-constrained randomization [30] taking into account the number of bacteriologically confirmed TB cases from that cluster the previous year. The randomization was performed by a statistician from the central research team 3 months prior to the start of inclusions. Participants, healthcare providers, study staff, and investigators are not blinded to the allocation of the health facilities.

The cluster list can be found in the Supplementary Material.

Criteria to discontinue the allocated intervention to a cluster are the absence of recruitment in a cluster for more than 2 months or if the NTP proposes a similar intervention that would bias the outcomes of the study.

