### Sample size calculation

For the sample size calculation, we used an estimated 60% completion rate among the eligible children in the facility-based arm based on a recent systematic review [35] and a 10% difference in the community-based arm, considered to be the minimal clinically relevant difference. We considered a cluster coefficient variability of 50% based on the variation in the number of bacteriologically confirmed index cases between the 20 clusters in the year prior to the intervention. An intra-cluster correlation of 0.01 was used. With these parameters, we would need to include at least 1500 declared child contacts by the index case who would be eligible to the TPT to have a power of 85%. With a minimum of 1500 enrolled child contacts, we could maintain at least 80% of power to detect a difference of 10% in the primary outcome between the two arms assuming the proportion with the primary outcome in the control arm ranges from 60 to 70% and of the cluster coefficient variability varies from 50 to 70%. The type I error rate *α* is conventionally fixed at 0.05%. Based on national household statistics per country [36–38], we make the hypothesis of one child under 5 years per household. Looking at the index case TB registrations in the year prior to the intervention, we estimate that it would be possible to include 1500 contact children in a 15-month period. Research assistants in each cluster supervised that all bacteriologically confirmed index cases registered in the NTP treatment register were screened for study eligibility to achieve adequate participant enrolment to reach sample size.

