### Statistical analysis

#### Primary analysis

The denominator for the analysis of the primary endpoint is the number of child contacts < 5 years and HIV-infected 5–14 years declared by the index case at the facility during the inclusion visit. Since discrepancies can be expected between what is declared by the index case and what is observed during contact screening, a sensitivity analysis will be performed using as denominator the number of children < 5 years of age and HIV-infected children of 5–14 years of age identified during the screening. An additional sensitivity analysis will be performed including only participants that followed all study procedures (per-protocol approach) among the declared and then enrolled child contacts. Dropping out of the cascade of cares and potentially being lost to follow-up can be the consequence of the models of care under evaluation. Therefore, lost to follow-up will be kept in the primary outcome analysis. They will be removed from the sensitivity per-protocol analysis.

A generalized linear mixed model with a binomial distribution and logit link function will be used to perform individual-level analysis adjusting for clustering. The regression model will include the fixed effect of treatment assignation and country and one random-effect for the cluster. A degree-of-freedom correction will be applied (between-within method) to deal with the type I error inflation due to the small number of clusters. The primary analysis will focus on the difference between the two study arms adjusted for country, and a secondary analysis will add an adjustment for unbalanced factors (urban/rural, district size) identified in the baseline assessment. For the analysis of the secondary outcomes, a similar mixed model will be used with the same random effects and correction method, focusing on each endpoint of the cascade of care for initiation and completion of TPT and each endpoint of the cascade of care for TB detection. The same model will be applied for the sensitivity analyses.

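### The primary model omits the index-case count on which randomisation was constrained; if that count is prognostic, the test is conservative and some power is forgone

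*Protocol article*

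**What the plan says.** The abstract (Methods/design) states: "Randomization was stratified by country and constrained on the number of index cases per cluster". The section Cluster selection and randomization gives the detail: within each country the 10 clusters were "allocated to one of the study models by a covariate-constrained randomization", and the constraining variable is the cluster's number of bacteriologically confirmed TB cases in the previous year. The Strengths section presents this constraint as the way variability between clusters is dealt with.

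Under Primary analysis the model is fixed term by term: "The regression model will include the fixed effect of treatment assignation and country and one random-effect for the cluster". A between-within degree-of-freedom correction is applied because there are few clusters. A secondary analysis adds factors found to be out of balance at the baseline assessment, with urban/rural setting and district size as the ones listed. Secondary outcomes use a similar model and the sensitivity analyses use the same one. No model names the index-case count.

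**The concern.** Two variables shaped the allocation: country, as a stratification factor, and the prior-year case count, as the constraint. The model keeps the first and drops the second. The secondary analysis is unlikely to restore it, since it is aimed at imbalanced factors and the constraint exists to keep the count balanced.

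Constraining on a prognostic covariate removes chance imbalance in that covariate from the treatment contrast, so the estimate varies less over the allocations that could have been drawn. A model without the covariate does not register this. The variation that the covariate explains stays in the estimated between-cluster variance and so in the standard error. The interval is then wider than it needs to be and the test rejects too rarely. The Limitations section says that more than 20 clusters could not be selected, so the efficiency of the analysis matters here.

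**Working it through.** **Inputs from the protocol (Sample size calculation, unless noted)**

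- Control arm: "we used an estimated 60% completion rate among the eligible children in the facility-based arm". Effect: "a 10% difference in the community-based arm, considered to be the minimal clinically relevant difference", read as 0.60 against 0.70.
- "We considered a cluster coefficient variability of 50% based on the variation in the number of bacteriologically confirmed index cases between the 20 clusters": CV = 0.5.
- "An intra-cluster correlation of 0.01 was used".
- N = 1500 in 20 clusters allocated 1:1, hence a mean of m = 75 children per cluster and 750 per arm. Stated power is 85%.
- Type I error is printed as 0.05%. It is read as 0.05, two-sided, because the literal value would give a power of only about 0.29.

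**Reproducing the stated power**

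1. Design effect = 1 + ((CV² + 1)m − 1) × ICC = 1 + (1.25 × 75 − 1) × 0.01 = 1.9275.
2. Effective size per arm = 750 / 1.9275 = 389.1.
3. SE = √((0.60 × 0.40 + 0.70 × 0.30) / 389.1) = √(0.45 / 389.1) = 0.0340.
4. z = 0.10 / 0.0340 = 2.94. Power = Φ(2.94 − 1.96) = 0.837, within two points of the stated 85%.
5. With a t reference on 17 df (20 clusters less intercept, arm and country) the power is 0.791; with 16 df it is 0.788.

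Nothing in this calculation uses the constraint.

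**Effect of leaving the count out**

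The protocol gives no figure for the association between count and outcome, so it was varied in a simulation of 2000 runs per scenario. Assumptions that are not in the documents:

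- lognormal counts with CV 0.5, and enrolment proportional to the count;
- in each country, an allocation drawn from the best-balanced 10% of the 252 possible 5:5 splits;
- a linear effect of the count on the proportion, explaining a share R² of the between-cluster variance;
- analysis by a cluster-level REML random-effects model, as an approximation to the planned logistic mixed model. It has arm and country (17 df), then the same plus the count (16 df).

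Results at ICC 0.01:

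| R² | Type I error, without count | with count | Power, without count | with count |
|---|---|---|---|---|
| 0 | 0.058 | 0.054 | 0.80 | 0.79 |
| 0.10 | 0.049 | 0.049 | 0.80 | 0.81 |
| 0.25 | 0.039 | 0.043 | 0.81 | 0.84 |
| 0.50 | 0.026 | 0.042 | 0.79 | 0.87 |
| 0.75 | 0.022 | 0.038 | 0.80 | 0.92 |

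Monte Carlo error: √(0.8 × 0.2 / 2000) = 0.009 for power and √(0.05 × 0.95 / 2000) = 0.005 for type I error.

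The mechanism shows at R² = 0.50. Without the count, the mean model SE is 0.0339 against an actual standard deviation of 0.0307, a ratio of 1.10. With the count it is 0.0296 against 0.0302, a ratio of 0.98. The two estimates have nearly the same actual spread (0.0307 and 0.0302). The randomisation has already delivered the precision, and the model without the count does not report it.

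**The case against.** **The harm is conditional.** This is the strongest counter-argument, and it stands. Nothing in the protocol shows that the case count predicts completion of preventive therapy. At R² of 0 or 0.10 the two models cannot be told apart, and at 0.25 the gain is about three points. Country is already adjusted for and takes up the main documented contrast, district hospitals against primary health centres. Some Ugandan clusters reach the required count only by pooling two facilities, so the count there partly reflects how clusters were assembled. That pooling can also be read the other way, since the Limitations section expects it to add heterogeneity in outcome measurement.

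**A reader might infer that the omission costs the trial its planned power.** The documents do not support that. The sample size takes no credit for the constraint, and simulated power without the count stays at 0.79 to 0.81 for every R², matching the 0.791 from the planning formula with 17 df. The distance from there to the stated 85% comes mostly from the t reference, not from the missing covariate.

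**A reader might infer that the planned test is invalid, or that the standard error ignores all of the balance gained.** Neither follows. The error is on the conservative side, with no bias and no excess of false positives. To the extent that the constraint makes the arms similar in size, that benefit enters the standard error without adjustment. Only a prognostic component can be missed.

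**A reader might infer that the count could never enter the secondary model.** That is too strong. A constraint limits imbalance without excluding it, and district size, which the article does not define, may overlap with volume. The count is nevertheless not named.

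Larger gaps appear at higher intra-cluster correlations: 0.40 against 0.50 at R² = 0.25 with an ICC of 0.05. That is five times the planned value and should not be taken as the expected size.

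**Conclusion.** The omission is plain in the text: the constraining variable is in the design and in no named model. Its consequence depends on an association that the protocol does not report. If the count explains 25% to 50% of between-cluster variance, about 3 to 8 points of power are forgone at the planned ICC, and the type I error without the count falls to 0.039 and 0.026. If it explains 10% or less, nothing measurable is lost. The figures rest on the assumed tightness of the constraint, the assumed R², a linear count effect and a cluster-level approximation to the logistic model.

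This is an avoidable inefficiency in the primary test, not a threat to its validity. The change is still worth making, because the possible gain clearly exceeds the small cost when the count turns out not to matter.

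**What to change.** Before the endpoint data are analysed, pre-specify the prior-year number of bacteriologically confirmed TB cases as a cluster-level fixed effect in the primary model, alongside arm and country. Use the form in which it entered the constraint, or its logarithm, and fix that choice in advance. State the between-within degrees of freedom as 16, and carry the term into the secondary-outcome models that reuse this form. Keep the country-only model as a sensitivity analysis. A randomisation test over the constrained set of allocations is an alternative that respects the design, provided that set can be reproduced.

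Cost: the count was used for the randomisation, so it is already held for all 20 clusters and no new data are needed. One degree of freedom is spent (17 to 16). If the count is unrelated to the outcome, up to about one point of power is given up: 0.3 points by the planning formula (0.791 to 0.788) and 1.2 points in the simulation (0.8035 to 0.7915).

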### Limitations

Because the cluster sites were limited to the facilities supported by the CaP TB project, it was not possible to select more than 20 clusters. It was impossible to avoid urban facilities, which increases the inter-cluster variability and may increase the risk of cluster contamination due to the more complex system of patients’ reference in cities as compared to rural settings. The proportion of urban clusters is higher in Cameroon as the two selected regions where the CaP TB project takes place include the two biggest cities of the country. In Uganda, some clusters comprise two health facilities to allow for the necessary recruitment capacity and this operational limitation may introduce more heterogeneity in the measurement of the outcomes.

Another limitation is the reliability of source documents from facility registers as compared to study-specific source documents, which can induce an information bias and risk of missing data. To minimize this limitation, a register data quality check was done during the baseline period and in sites where inconsistencies were found, a training on data collection was recommended.

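### Urban/rural is treated as a source of variability between clusters but was left out of both the randomization constraint and the primary model, leaving the main estimate open to chance imbalance and avoidable loss of precision

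*Protocol article*

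**What the plan says.** All references are to the protocol article.

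- **Primary model** (Primary analysis): "The regression model will include the fixed effect of treatment assignation and country and one random-effect for the cluster". The small number of clusters is handled as follows: "A degree-of-freedom correction will be applied (between-within method) to deal with the type I error inflation due to the small number of clusters".
- **Urban/rural** (same section): it is kept for later, where "a secondary analysis will add an adjustment for unbalanced factors (urban/rural, district size) identified in the baseline assessment".
- **Allocation** (Cluster selection and randomization): stratified by country, with ten clusters in each, and constrained "taking into account the number of bacteriologically confirmed TB cases from that cluster the previous year". No other constraint is named.
- **Site selection** (same section): "Priority was given to rural, semi-rural, or semi-urban facilities as there is less population movement than in an urban setting".
- **Limitations**: "It was impossible to avoid urban facilities, which increases the inter-cluster variability". The same sentence adds a possible risk of contamination. The next one says that urban clusters are proportionally more common in Cameroon.

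**The concern.** The article names urban setting as something that makes clusters differ, and it knew each cluster's setting before enrolment. It then used that knowledge neither in the allocation nor in the primary model.

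Population movement could plausibly bear on the endpoint, which requires both starting and completing preventive therapy, since "lost to follow-up will be kept in the primary outcome analysis". That link is an inference; the article does not state it.

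The rule for choosing covariates is also weak. A covariate earns its place in a model by being prognostic, not by looking unbalanced. Under the stated rule a prognostic factor is adjusted for only if the draw was unlucky, and even then only outside the main result.

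At stake is a main estimate that is noisier than it need be. If the country-only and adjusted results disagreed, the one more exposed to the draw would be the primary result.

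**Working it through.** **Inputs from the article (Sample size calculation):** 60% completion in the facility arm; 10-point difference, so 60% vs 70%; ICC 0.01; cluster-size coefficient of variation 0.5; 1500 children in 20 clusters, so 75 per cluster and 750 per arm; stated power 85%. I read the type I error as two-sided 0.05. The printed 0.05% would give about 29% power and cannot be what was used.

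**Assumed, not in the article:** the share of between-cluster variance due to urban/rural, the fraction of urban clusters, and their split between arms.

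**1. The plan's own figure.** Design effect = 1 + ((0.5² + 1) × 75 − 1) × 0.01 = 1.93. Effective size = 750 / 1.93 ≈ 389 per arm. Power by the normal approximation is 83.4%, close to the stated 85%.

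**2. With the planned degrees of freedom.** SE = √[(0.24 + 0.21) / 389] = 0.0340, and 0.10 / 0.0340 = 2.94. With arm and country in the model there are 20 − 3 = 17 between-cluster df (critical t 2.110). Noncentral-t power is 79.1%.

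**3. Effect of leaving urban/rural out, over all randomizations.** Cluster-level simulation, 6000 runs per scenario, stratified allocation ignoring the case-number constraint. Assumed: 5 of 10 clusters urban in Cameroon and 2 of 10 in Uganda, with the urban effect added to an ICC of 0.01.

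| Urban effect | Type I error, country only | Mean error of estimate, country only | SD, country only | SD, with urban/rural |
|---|---|---|---|---|
| 0 points | 5.0% | about 0 | 0.037 | 0.038 |
| 5 points | 5.0% | about 0 | 0.038 | 0.038 |
| 10 points | 5.3% | about 0 | 0.043 | 0.038 |

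The planned test is valid. The loss is in precision, and only if the urban effect is large.

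**4. Shift given a particular draw.** Between-cluster SD = √(0.01 × 0.24) = 0.049. If a share s of that variance is due to urban/rural and a fraction q of clusters is urban, the urban–rural gap is √s × 0.049 / √[q(1 − q)]. At q = 0.4–0.5 this is about 5 points for s = 25% and 7 points for s = 50%. With five clusters per arm in each country, the country term does not alter the shift, which is gap × difference in urban proportion:

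- 2 in 10: 5 × 0.2 = 1.0 and 7 × 0.2 = 1.4 points
- 4 in 10: 2.0 and 2.8 points

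**5. How often.** I tried five assumed urban counts, from 3 of 10 in Cameroon and none in Uganda up to 6 and 3, again ignoring the case-number constraint. The arms differ by two or more urban clusters in 17–63% of allocations and by four or more in 0–14%.

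**6. Effect of adjusting.** One two-level covariate leaves 16 df (critical t 2.120).

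- Not prognostic, arms balanced on it: 78.8%, a loss of 0.3 points.
- Explains 25% (residual ICC 0.0075, design effect 1.70), balanced: 84%.
- Explains 50% (residual ICC 0.005, design effect 1.46), balanced: 89%.
- Explains 50%, 4-in-10 imbalance: variance inflation = 1 / (1 − 0.16) = 1.19 at q = 0.5, power about 82–83%.
- Not prognostic, 2-in-10 or 4-in-10 imbalance: variance inflation 1.04 or 1.19, power about 77% or 72%.

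These figures are on the risk-difference scale. The planned model is logistic, so they are approximations.

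**The case against.** The strongest reply is that the primary analysis is valid as planned. Adjusting for the stratification factor in the primary model and for other factors in a secondary one is an accepted choice. Both factors are named in advance and tied to a baseline phase that precedes enrolment, so they are not picked on outcomes. All of this stands, and step 3 confirms it.

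A reader might infer more: that the article admits an imbalance between arms and so keeps a known confounder in its main estimate. The documents do not support that.

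- They give no urban counts by arm and no effect of urban setting on completion.
- The only imbalance stated with a direction is between countries, and country is both a stratum and a term in the primary model.
- The word unbalanced is not said to mean between arms.
- After randomization, any imbalance between arms is due to chance.

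A reader might also quote a type I error of about 10–12% and power of about 52–55%. These hold only if urban/rural explains half the between-cluster variance and the arms differ by 4 in 10. The power figure further needs the imbalance to go against the intervention.

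Variability between clusters may also refer to caseload, since the Strengths section says that the constraint on index-case numbers addresses it. That reading is possible. But the Limitations sentence goes on to patient referral in cities and contamination, and the same paragraph ends on heterogeneity in outcome measurement, so it is not clearly about caseload alone.

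Lastly, district size might look ill-suited in Uganda, where "the ten clusters were primary health centers in four districts in the South West region". The article does not define the variable, its coding belongs to the analysis plan, and it is already outside the primary model. Nothing is raised on it here.

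**Conclusion.** The point holds as a weakness in how the covariates were fixed, not as a bias. A cluster characteristic that the article itself treats as relevant, and that was known before enrolment, is neither constrained at allocation nor in the primary model, and is chosen for a secondary model by a poor criterion. Validity over all randomizations is intact.

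What remains is exposure to the draw, about 1.0–1.4 points for a 2-in-10 imbalance if urban/rural explains 25–50% of the between-cluster variance, and forgone power. Under the same shares, adjustment would give about 84–89% with the arms balanced on it, against 79.1% as planned. The shares, the urban fraction and the imbalance are all assumptions, so the true size and direction cannot be derived from the article. The change is worth making because it is cheap, not because the plan is invalid.

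**What to change.** In the Primary analysis section:

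1. Put urban/rural in the primary model as a fixed cluster-level covariate with arm and country, whatever the observed balance, and state its coding.
2. Report the model with arm and country only as the sensitivity analysis.
3. Remove imbalance as the criterion for choosing covariates.

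This is a wording change, to be made before outcome data are analysed by arm; each cluster's setting is already known. With two levels the cost is one between-cluster df (17 to 16), about 0.3 points of power if urban/rural is not prognostic and the arms are balanced on it. If they are imbalanced, variance inflation adds to that, as in step 6. The article describes four kinds of setting; coding all four would leave 14 df (about 78.1% on df alone), so two levels are preferable.
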